### Study population

We aim to enrol 250 patients, divided into two groups with minimum 125 patients per group: COVID group and non-COVID group. Both groups will be monitored at 6, 12 and 24 months since the first procedure visit, defined as the baseline.

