**Assessments**					
*Clinical data*	*X*	*X*	*X*	*X*	*X*
*IL1, IL6, VCAM-1, endoglin, NO and ADMA*		*X*	*X*	*X*	*X*
*CV risk*			*X*	*X*	*X*
*Mortality rate*					*X*
*Renal outcome*			*X*	*X*	*X*
*ED*					*X*

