Echocardiography	- according to the American Society of Echocardiography recommendations by an observer unaware of the LUS and bioimpedance results; - measurements: cardiac anatomy (e.g. volumes, geometry, mass) and function (e.g. left ventricular function, valvular function, right ventricular function, and pulmonary artery pressure); - in patients with adequate acoustic windows, both left ventricular global longitudinal strain (LVGLS) and right ventricular free wall strain (RVFWS) will be calculated.
LUS	- patient in the supine position; - measurements of the anterior and lateral chest on both sides of the chest, from the second to the fourth (on the right side to the fifth) intercostal spaces, at parasternal to mid-axillary lines; - B-lines will be recorded in each intercostal space and were defined as a hyperechoic, coherent US bundle at narrow basis going from the transducer to the limit of the screen; − B-lines starting from the pleural line can be either localized or scattered to the whole lung and be present as isolated or multiple artifacts; - the sum of B-lines produces a score reflecting the extent of lung water accumulation (0 being no detectable B-line).
BIS	- portable whole-body multi-frequency bioimpedance analysis device (BCM®Body Composition Monitor – Fresenius Medical Care D GmbH); - electrodes will be attached to the patient’s forearm and ipsilateral ankle, with the patient in a supine position; - measurements: body resistance and reactance to electrical currents of 50 discrete frequencies, ranging between 5 and 1000 kHz; - calculations: ECW, ICW and TBW, to determine the amount of fluid overload; - AFO is defined as the difference between the expected patient’s ECW under normal physiological conditions and the actual ECW, whereas RFO is defined as the absolute fluid overload AFO to ECW ratio.
Blood collection for biomarker evaluation	- whole blood will be collected in gel & clot activator tubes (minimum 3.5 mL tube) at each intervention visit for each patient; - serum will be collected by centrifugation and frozen in aliquots at −80 ° C until further analysis; - IL1, IL6, VCAM-1, endoglin, NO and ADMA in serum samples will analysed by specific enzyme linked immunosorbent assay (ELISA) kits on a Sunrise Basic Tecan microplate reader.

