### Outcome data

***The primary outcomes of this study*** will be all-cause mortality rate, a composite CV outcome (time to first non-fatal myocardial infarction, non-fatal stroke, and hospitalization for heart failure or CV death) and long-term impact of the COVID-19 on markers of CV risk and ED in all included patients.

***Secondary outcomes*** are defined as a composite of renal outcome: doubling of creatinine or a 40% decline in eGFR or dialysis initiation in CKD or KTx patients.

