### Statistical analysis

The statistical analyses will be performed using the SPSS for Windows, version 19.0.1, R (version 3.1.2) package for statistical analysis and STATA 13. Non-normally distributed variables will be expressed as median with interquartile range and normally distributed variables as mean ± SD, as appropriate. Between-group comparisons will be assessed for nominal variables with the Chi-square test, and by Kruskal-Wallis test or one-way ANOVA for the rest of the variables. In order to comply with the assumptions for regression analysis, logarithmic conversion will be performed for non-normally distributed variables. Pearson correlation coefficient will be used to determine correlations between variables. Stepwise multivariate regression analysis including all univariate associates (*p* < 0.05) will be used to assess the independent associations between variables. Survival and time-to-event analysis of outcomes will be performed using Kaplan-Meier cumulative survival plots and Cox proportional hazards model, including adjustment for potential confounding factors. In the multivariate Cox models, we will adjust for all variables that will be correlated to the study outcomes with *P* < 0.05 at univariate Cox analyses.

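### Cardiovascular-risk and endothelial markers are a primary outcome measured at four visits, but the stated methods ignore the repeated measurements and give no test of whether a group difference persists or recovers

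*Protocol article*

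**What the plan says.** Outcome data in the protocol article lists among the primary outcomes the "long-term impact of the COVID-19 on markers of CV risk and ED in all included patients". Study population sets the schedule: "Both groups will be monitored at 6, 12 and 24 months since the first procedure visit, defined as the baseline". Table 1 marks FMD, arterial stiffness, intima-media thickness, echocardiography, lung ultrasound, bioimpedance and blood collection at all four visits, and likewise "IL1, IL6, VCAM-1, endoglin, NO and ADMA". The ED row of the same table is marked at 24 months only.

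Statistical analysis assigns the chi-square test to nominal variables and compares groups "by Kruskal-Wallis test or one-way ANOVA for the rest of the variables". It adds Pearson correlation and "Stepwise multivariate regression analysis including all univariate associates" with an entry rule of p < 0.05. To meet regression assumptions, "logarithmic conversion will be performed for non-normally distributed variables". Kaplan-Meier and Cox methods cover the time-to-event outcomes. No primary visit is set for the markers, and no listed method has a term for repeated visits.

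Table 2 defines the lung ultrasound score as a sum of B-lines, "0 being no detectable B-line", and absolute fluid overload as the difference between expected and actual extracellular water.

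**The concern.** The article's Discussion cites impaired FMD still present 3 months after the acute illness, and mixed evidence on whether ventricular function recovers. Persistence against recovery is therefore the natural question for these markers. Statistically it is a group x visit question, and no listed method addresses it.

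The stated tests can be applied in two ways. Testing each visit separately gives up to four unconnected results per marker and no test of change. Pooling the visits treats up to four values from one patient as independent, which understates the standard error of a group difference.

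Two smaller matters sit beside this. The ED row at 24 months does not fit an outcome defined for every included patient, because those who die earlier have no 24-month value. And the log rule cannot be applied to a variable that takes the value zero or less.

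**Working it through.** **1. Schedule against method.** FMD, VCAM-1, endoglin, NO and ADMA are taken four times per patient. Kruskal-Wallis and one-way ANOVA take one independent value per patient, as do Pearson correlation and ordinary regression. A change score entered into one-way ANOVA would compare two chosen visits, but the plan defines no change score and no pair of visits.

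**2. The plan's own figure.** Sample size: 9% v 22% mortality, alpha 0.05 (two-sided assumed), 80% power, 125 per group. With pooled variance and mean rate 0.155:

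n = [1.96 x sqrt(2 x 0.155 x 0.845) + 0.842 x sqrt(0.09 x 0.91 + 0.22 x 0.78)]^2 / 0.13^2 = 121 per group.

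At 125 per group the power is 81.4%, so the figure is sound. It concerns mortality only and says nothing about the markers.

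**3. If ED means the 24-month value.** Assume that the 9% and 22% apply at 24 months (the plan gives no time horizon):
- COVID group: 125 x 0.78 = 97.5
- non-COVID group: 125 x 0.91 = 113.75
- without a value: 38.75 of 250 = 15.5%, split 22% v 9%.

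The detectable difference at 80% power is 2.80 x sqrt(2/125) = 0.354 SD with everyone, and 2.80 x sqrt(1/97.5 + 1/113.75) = 0.387 SD in survivors.

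**4. What four visits add to precision.** The within-patient correlation rho is not in the document. Compound symmetry is assumed.

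*Time-averaged group difference, complete data.* Variance relative to one visit = (1 + 3 rho)/4:
- rho 0.5: 0.625
- rho 0.6: 0.70
- rho 0.8: 0.85

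The detectable difference becomes 0.354 x sqrt(0.625) = 0.28 SD at rho 0.5 and 0.354 x sqrt(0.85) = 0.33 SD at rho 0.8.

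*Difference at one visit, complete data.* With unstructured covariance and the same covariates at each visit, the mixed model reproduces the separate-visit contrasts. There is no gain.

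*Difference at 24 months, with the deaths of step 3.* Take rho 0.6 and all three earlier visits observed. The share of 24-month variance explained by the earlier visits is R2 = 3 x 0.36 / (1 + 2 x 0.6) = 0.49.
- survivors only: 1/97.5 + 1/113.75 = 0.01905
- mixed model: 0.51 x 0.01905 + 0.49 x (2/125) = about 0.0176

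That is about 8% lower.

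**5. Possible survivor bias.** Assume a true difference of -0.40 SD (a lower marker is worse), the mortality of step 3, and a logistic link between marker and death:

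| Odds ratio of death per SD lower marker | Difference in survivors | If there is no true difference |
|---|---|---|
| 1.0 | -0.40 | 0 |
| 1.5 | -0.35 | +0.05 |
| 2.0 | -0.32 | +0.08 |
| 3.0 | -0.29 | +0.11 |

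The odds ratios are assumptions. The document gives a direction only, for FMD in acute COVID-19.

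**6. Log rule.** log(0) is undefined, and 0 is a valid B-line score. Absolute fluid overload is a signed difference and relative fluid overload is its ratio to extracellular water, so both can be zero or negative.

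**The case against.** The strongest reply is that this is a condensed article and that covariance structures, count models and the treatment of zeros normally belong in an analysis plan that is not shown. That holds for the details. It does not cover the main point: the section goes down to software versions and p-value entry rules, and the methods it names for a primary outcome are cross-sectional. The planned multivariable regression means that one-way tests are not the whole plan, but it ignores repeated visits just the same.

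Several stronger readings are tempting and are not supported:

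- *That ED is studied only in 24-month survivors.* Table 1 schedules FMD and the endothelial biomarkers at every visit, so patients who die after baseline still contribute ED data. Mortality is also marked at 24 months only, which suggests that the column may show when a derived outcome is evaluated. What stands is a row to reconcile.
- *That a mixed model is worth a 43% larger sample.* This is 1/0.70 at rho 0.6. It belongs to a four-visit average with complete data, not to per-visit differences.
- *That the comparison is biased towards no effect.* This needs the 24-month reading, mortality rates that apply at that time, and markers that predict death. The illustration runs from 0 to 0.11 SD.
- *That logging removes the healthiest patients.* The rule is confined to regression and to non-normal variables, Kruskal-Wallis accepts zeros, and nothing says that zeros are dropped. Only the B-line score and fluid overload are shown to be affected.

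**Conclusion.** The point stands in a limited form and should be corrected. The analyses fixed for a primary marker outcome ignore the four-visit structure, give no test of group x visit, and would be invalid if visits were pooled. This rests on the stated methods and schedule and needs no outside assumption.

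The ED row at 24 months and the outcome definition conflict if that row is the endpoint. The size, about 98 v 114 of 125, depends on the plan's mortality rates applying at 24 months. The log problem is real but minor.

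The gain from the change is mainly a valid test of change and the use of data from patients who later die. The added precision is uncertain: substantial for a time-averaged contrast at moderate correlation, and small (about 8% in variance at rho 0.6 with the assumed deaths) for the 24-month contrast.

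**What to change.** 1. Analyse each continuous marker with a linear mixed model. Use all four visits as responses, fixed effects for group, visit, group x visit and the matching factors (age, sex, kidney disease category), and an unstructured within-patient covariance.
2. Report the group x visit test, the difference at each visit and, if one summary is wanted, the time-averaged difference.
3. Do not adjust for the baseline marker. By the inclusion criteria that visit falls at least 2 weeks after the positive test in the COVID group, so adjustment could remove part of the effect under study.
4. Add a sensitivity analysis that ranks deaths as the worst outcome. The mixed model does not itself resolve truncation by death: treating values after death as missing at random describes what would be seen had nobody died.
5. Mark ED at all four visits in Table 1 and reconcile the row with the primary outcome definition.
6. In regression, leave fluid overload unlogged and use a count model for the B-line score, such as a negative binomial model with a patient effect.

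The cost is analysis wording and one table row. The measurements are already scheduled, and the named software can fit these models.

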### Sample size power calculation

According to sample size power calculations, including 125 patients in each group will provide statistical power (alpha 0.05 and power 80%) for an estimated difference in the mortality rate of 9% [29] in the non-COVID group compared to 22% mortality in the COVID positive group [30–34].

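### Kaplan-Meier curves for the renal and CV composites would overstate absolute risk by about 1 to 2 points, more in the COVID group, because deaths outside each composite can only be censored

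*Protocol article*

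**What the plan says.** The Statistical analysis section of the protocol article gives one sentence on time-to-event methods: "Survival and time-to-event analysis of outcomes will be performed using Kaplan-Meier cumulative survival plots and Cox proportional hazards model", with adjustment for confounders. It does not say which outcomes are meant, names no other estimator of incidence over time, and gives no rule for deaths that are not part of an endpoint.

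The Outcome data section lists three outcomes that this sentence could cover:

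- All-cause mortality (primary).
- The CV composite (primary): "a composite CV outcome (time to first non-fatal myocardial infarction, non-fatal stroke, and hospitalization for heart failure or CV death". CV death is an event; non-CV death is not.
- The renal composite (secondary): "doubling of creatinine or a 40% decline in eGFR or dialysis initiation in CKD or KTx patients". No death is an event.

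The Sample size power calculation section assumes an "estimated difference in the mortality rate of 9% [29] in the non-COVID group compared to 22% mortality in the COVID positive group", and gives no time horizon for either figure. The Study population section sets the follow-up: "Both groups will be monitored at 6, 12 and 24 months since the first procedure visit, defined as the baseline".

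**The concern.** A patient who dies without a renal event can no longer have one. Kaplan-Meier has no state for this. It removes the patient from the risk set as censored, which assumes that the patient would have gone on to have events at the same rate as those still alive. The resulting 1-KM curve describes risk in a setting without death and lies above the proportion of patients who actually reach the endpoint. The gap widens with the death rate.

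The study is sized on the expectation that more than twice as many patients die in the COVID group as in the control group. The inflation would therefore differ between groups and would push the COVID curve up by more, in the direction of the study hypothesis. What is at stake is the absolute renal and CV risk read from the curves, and the difference between groups read from them.

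**Working it through.** **Plan's own figure.** For 9% against 22% mortality with 125 per group and two-sided alpha 0.05 (the article does not state sidedness), the pooled two-proportion formula uses a mean proportion of 0.155:

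- (√125 × 0.13 − 1.96 × √(2 × 0.155 × 0.845)) / √(0.09 × 0.91 + 0.22 × 0.78) = 0.894, which is a power of 81.4%.

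The stated 80% is reproduced. This calculation concerns all-cause mortality, which has no competing event.

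**Inputs for the competing-risk check.**

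- Mortality 9% and 22%: from the sample size section. Assumed to apply over 24 months, to the CKD/KTx patients in the renal composite, and with a death rate that does not depend on the renal event.
- Constant hazards: assumed.
- Renal and CV event risks: not in the article, so a range is used.
- Share of deaths that are non-CV: not in the article; 30% to 70% is used.

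**Formulas.** With cumulative hazards Le (event) and Ld (competing death) over the period:

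- 1-KM = 1 − exp(−Le)
- cumulative incidence = Le/(Le + Ld) × (1 − exp(−(Le + Ld)))

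**Renal composite, all deaths competing, 1-KM of 20%.** Le = −ln(0.80) = 0.2231.

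- Non-COVID: Ld = −ln(0.91) = 0.0943. Cumulative incidence = 0.7029 × 0.2720 = 19.1%. Overstatement 0.9 points.
- COVID: Ld = −ln(0.78) = 0.2485. Cumulative incidence = 0.4732 × 0.3760 = 17.8%. Overstatement 2.2 points.

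Over a range of 1-KM values:

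| 1-KM | Cumulative incidence, non-COVID | Cumulative incidence, COVID |
|---|---|---|
| 10% | 9.6% | 8.9% |
| 20% | 19.1% | 17.8% |
| 30% | 28.7% | 26.8% |
| 40% | 38.3% | 35.8% |

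The relative overstatement is about 4-5% (non-COVID) and 12-13% (COVID) throughout.

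**Reverse direction.** Fix the true cumulative incidence at the same value in both groups and solve for 1-KM:

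| True incidence, both groups | 1-KM, non-COVID | 1-KM, COVID | Spurious difference |
|---|---|---|---|
| 10% | 10.5% | 11.3% | 0.8 points |
| 20% | 20.9% | 22.5% | about 1.6 points |
| 30% | 31.3% | 33.6% | 2.3 points |

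**Sensitivity to the mortality assumption.** With both figures halved (4.5% and 11%), a true 20% in both groups plots as 20.4% and 21.1%, a spurious difference of 0.7 points.

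**CV composite, only non-CV deaths competing.** With half of deaths non-CV, Ld is halved to 0.0472 and 0.1242. A 1-KM of 20% then corresponds to 19.6% and 18.9%, an overstatement of about 0.5 and 1.2 points. With non-CV shares of 30% to 70% and 1-KM of 10% to 40%, the overstatement is 0.1-1.2 points (non-COVID) and 0.4-3.0 points (COVID).

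**The case against.** - **The article never says that deaths are censored.** Correct: this is inferred from the method. A journal article may also leave event handling to an analysis plan that is not shown. However, a standard Kaplan-Meier curve can do nothing else with a death outside the endpoint. The point therefore rests on a method that the article fixes, not on a missing detail.
- **The renal composite might be compared as proportions at visits.** Only the CV composite is worded as a time to first event. Table 1 schedules the renal outcome at 6, 12 and 24 months, and chi-square tests are also planned. This reading is possible. The time-to-event sentence nevertheless covers the outcomes without exception.
- **The Cox comparison is sound.** This stands. With deaths censored, the Cox model gives a valid cause-specific hazard ratio, a standard choice for asking whether prior COVID-19 affects CV and renal events. A reader might infer that the hazard ratios, the mortality comparison or the sample size are biased too; nothing in the article supports that.
- **Equal Kaplan-Meier curves do not show a false COVID excess.** Also correct. With 1-KM at 20% in both groups the plot shows no difference, and true incidence is lower in the COVID group. A spurious excess appears in the reverse case, where true incidence is equal.
- **The bias is small.** With 125 per group and 20% risk, the standard error of a difference is about √(2 × 0.2 × 0.8/125) = 5.1 points. A spurious 1.6 points is about a third of that (1.6/5.1 = 0.31). The renal subset is smaller than 125 per group, so its standard error is larger. This limits the importance of the point, but the bias is systematic and does not shrink with more patients.
- **The 22% may not describe deaths after enrolment.** The Study design section requires recovery from the acute illness, and the sample size section gives no horizon. The size of the bias is therefore conditional. Its direction within each group is not, provided some excluded deaths occur.

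**Conclusion.** The point holds for absolute risks read from Kaplan-Meier curves of the two composites. It bears mainly on the secondary renal composite, where every death competes, and less on the primary CV composite, where CV deaths are events.

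At a risk of 20%, the renal overstatement is about 0.9 points (non-COVID) and 2.2 points (COVID). The figures rest on the assumptions listed in the working: the 9% and 22% applying over 24 months and to the CKD/KTx subset, constant hazards, and an assumed non-CV share for the CV composite. The larger bias in the COVID group depends on mortality being higher there, as the sample size section expects.

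This is a modest reporting bias with a simple remedy. It is not a flaw that invalidates the planned comparisons.

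**What to change.** - Keep Kaplan-Meier for all-cause mortality.
- For the renal composite, plot Aalen-Johansen cumulative incidence with death from any cause as the competing event.
- For the CV composite, plot Aalen-Johansen cumulative incidence with non-CV death as the competing event.
- State the handling of these deaths in the analysis section, and label the Cox results for both composites as cause-specific hazard ratios. A Fine-Gray model is optional.

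Cost: a change of wording and slightly more analysis work. No additional patients, visits or measurements are needed, and the sample size does not change. Deaths must be classified as CV or non-CV, which the CV composite already requires.

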More and more studies are reporting the persistence of COVID-19 related symptoms for more than a month after the acute episode, recently defined as post-COVID syndrome*.* The percentage of incessant symptomatology varies from 35 to 89.2% [17, 18] and it is independently associated with age [17], two or more comorbidities and the severity of the acute disease [18–21]. It looks that women are more predisposed to experience remaining symptoms [22]. The laboratory abnormalities are also frequently reported. An increase in D-dimer, interleukin-6 (IL-6), C-reactive protein (CRP), fibrinogen level as well as lymphocyte count may serve as predictors for long COVID [23]. The percentage of renal transplant recipients who survived acute COVID-19 and had no clinical symptoms or were free from any laboratory abnormalities after 2 months from the initial diagnosis was 11.53%. Sustained clinical symptoms were found in 45.2%, and one or more laboratory abnormalities were reported in 71.2%. Long-term complications in these patients were strongly predicted by diabetes mellitus, hospitalization in the acute setting, renal allograft function, as well as laboratory abnormalities [24].

COVID-19 survivors have higher risks of AKI, de novo development or worsening of proteinuria, eGFR decline and progression to ESKD. These outcomes are reported even among patients those with mild symptoms and increase with the severity of the infection [25].

The underlying mechanisms of these manifestations and long-term complications are not completely understood, but emerging data emphasize the endothelium, as a central pillar in the long COVID conundrum, with implications in inflammation, the pro-thrombotic phenotype and disseminated intravascular coagulation [26]. Endothelial dysfunction (ED) refers to a systemic condition in which the endothelium loses its physiological properties, including the tendency to promote vasodilation, fibrinolysis, and anti-aggregation [13]. Morphologic findings from deceased patients confirm the presence of viral elements within endothelial cells and an accumulation of inflammatory cells, with evidence of endothelial and inflammatory cell death. Endotheliitis in several organs as a direct consequence of viral involvement and of the host inflammatory response may explain the impaired microcirculatory function in different vascular beds and clinical sequelae in patients with COVID-19 [27].

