### Objectives

The objectives of this observational study are to determine:the feasibility of flow mediated dilation (FMD), bioimpedance spectroscopy (BIS) fluid assessment, lung ultrasound (LUS) and pulse wave velocity (PWV) measurement in CKD patients following COVID-19 and matched CKD control-patients without a history of previous SARS-CoV-2 infection;the long-term impact of the COVID-19 on markers of CV risk and ED in patients with CKD and KTx on a composite CV outcome (time to first non-fatal myocardial infarction, non-fatal stroke, hospitalization for heart failure or CV death) and on all-cause mortality;the long-term impact of the COVID-19 on markers of CV risk and ED in patients with CKD and KTx on a composite renal outcome: doubling of creatinine or a 40% decline in eGFR or dialysis initiation.

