#### Inclusion criteria

Age > 18 years;Patients with CKD stage 3–5, including dialysis or KTx with confirmed COVID-19, at minimum 2 weeks after the confirmed test;Age, sex and kidney disease (CKD stage 3–5, dialysis or KTx) matched patients without confirmed SARS-CoV-2 infection.

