FMD is a widely recognized indicator of both subclinical atherosclerosis and coronary artery endothelial function [48], with important prognostic value [49]. Compared with healthy controls, significantly lower FMD values were reported during the acute phase of COVID-19 [50, 51]. In addition, FMD was an independent predictor of mortality in this setting [51, 52]. FMD was also assessed in the post-COVID population, with evidence suggesting the persistence of impaired FMD at 3 months distance after the acute event [53]. In a study that included 133 convalescent moderate-to-severe COVID-19 patients and 133 matched controls, FMD values were significantly lower within 2 months from COVID-19, and were directly correlated with the severity of pulmonary disease. However, this difference was nullified by female gender, smoking or the presence of more than 3 concomitant risk factors [54]. Thus, one can conclude that COVID-19 is an independent predictor of ED [55]. Interestingly, pulmonary rehabilitation increased FMD with ~ 2% among 82 patients with a history of severe or critical COVID-19 [56].

Arterial stiffness is a risk factor for in-hospital mortality in COVID-19 patients [57] and also for increased hospitalization duration [58]. PWV is also increased in patients with prior COVID-19 disease [59, 60].

The up-to-date review of Samprathi and Jayashree [61] presents the rational use of available biomarkers in the diagnosis and management of patients with COVID-19. The authors discuss based on Sars-CoV-2 pathophysiology, the laboratory tests offered to the clinician, from hematological, inflammatory, coagulative and biochemical parameters and up to cardiac biomarkers. The combined hematological biomarkers, namely increased leukocytes, neutrophils, CRP, PCT and ferritin, cytokine levels (IL-2R, IL-6, IL-8, IL-10 and TNF-α) and decreased lymphocyte counts predicts the severity of the disease and hospital admission. At inflammatory level, elevated CRP, PCT, cytokines (IL-6, IL-1b, IL-2, IL-8, IL-17, G-CSF, GMCSF, IP-10, MCP-1, CCL3, and TNFα) values forecast also, predicts progression to severe disease. Raised cardiac biomarkers involving CK, CK-MB, LDH, Mb, cTnI, α-HBDH, AST, and NT-proBNP were observed especially in severe illness and were associated with higher mortality. The proposed biomarkers play an essential role in early suspicion, diagnosis, monitoring, and recognition of acute complications, but what about on the long-term effects of COVID-19?

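### The Cox covariate rule does not exclude markers measured after infection, so the adjusted COVID hazard ratio may leave out whatever part of the effect runs through them

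*Protocol article*

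**What the plan says.** The Statistical analysis section plans Kaplan-Meier plots and a Cox model, "including adjustment for potential confounding factors". The next sentence gives the working rule: "In the multivariate Cox models, we will adjust for all variables that will be correlated to the study outcomes", with P < 0.05 in univariate Cox analyses as the entry threshold. It sets no condition on when a variable is measured or on whether it is related to COVID status, and it gives no list of candidates.

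Under Inclusion criteria, COVID patients enter "at minimum 2 weeks after the confirmed test". Study population defines baseline as the first procedure visit. Table 1 schedules FMD, arterial stiffness, intima-media thickness, echocardiography, lung ultrasound, bioimpedance and the serum markers from that visit onwards. In the COVID group every study measurement of these therefore follows infection.

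Outcome data lists all-cause mortality, the CV composite and the markers themselves as primary outcomes. One objective is worded as "the long-term impact of the COVID-19 on markers of CV risk and ED in patients with CKD and KTx on a composite CV outcome".

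**The concern.** Adjustment for confounding needs variables that are related to both exposure and outcome and are not consequences of the exposure. A screen on outcome association cannot tell a confounder from a mediator, so the rule does not enforce the purpose given in the sentence before it.

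The article itself suggests that some markers may be mediators. Background says that "emerging data emphasize the endothelium, as a central pillar in the long COVID conundrum". The Discussion reports that impaired FMD persists 3 months after the acute event, that "PWV is also increased in patients with prior COVID-19 disease", and that "FMD was an independent predictor of mortality in this setting". A marker that predicts death is the kind of variable that passes the screen. If COVID also shifts it, adjusting for it takes the mediated part out of the COVID hazard ratio.

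This matters because matching covers only age, sex and kidney disease category. The adjusted Cox model is the one planned time-to-event comparison of mortality and the CV composite that controls for other confounders.

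**Working it through.** **Inputs from the protocol article.** Sample size power calculation: mortality 9% (non-COVID) and 22% (COVID), 125 per group, alpha 0.05, power 80%. Study population: follow-up to 24 months. A two-sided test is assumed, since sidedness is not stated.

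**The plan's own figure.** Two-proportion test with pooled variance under the null, mean rate 0.155:
- SE under the null = √(2 × 0.155 × 0.845 / 125) = 0.0458
- SE under the alternative = √((0.09 × 0.91 + 0.22 × 0.78) / 125) = 0.0450
- z = (0.13 − 1.96 × 0.0458) / 0.0450 = 0.894, so power = 81.4%

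The stated 80% is reproduced.

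**The same design as time-to-event.**
- HR = ln(0.78) / ln(0.91) = 2.63
- expected deaths = 125 × (0.09 + 0.22) = 38.75
- Schoenfeld power = Φ(√38.75 / 2 × ln 2.63 − 1.96) = Φ(1.055) = 85.4%

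**Effect of the rule.** The documents give no mediated share, so it is an assumption, *m*, shown as a range. The effect not passing through the marker is HR = 2.63^(1 − m).

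Simulation: 125 per group, 24 months, 400 runs per setting. One standardised marker has an HR per SD of 1.5 or 2.0, and COVID shifts it by m × ln 2.63 / ln(HR per SD). Control mortality was calibrated to 9%. The marker entered the Cox model only if its univariate P was below 0.05. Ranges cover the two marker strengths.

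| Share *m* | 2.63^(1 − m) | Schoenfeld power | Marker admitted | HR and power, marker left out | HR and power under the rule |
|---|---|---|---|---|---|
| 0% | 2.63 | 85% | 70-98% | 2.52-2.59; 77-80% | 2.60-2.61; 81-82% |
| 25% | 2.07 | 62% | 88-99% | 2.57-2.61; 78-79% | 2.10-2.12; 53-55% |
| 50% | 1.62 | 33% | 93-99% | 2.47-2.48; 76-77% | 1.61-1.63; 20-24% |
| 75% | 1.27 | 11% | 95-100% | 2.41-2.50; 73-80% | 1.25; 7-10% |

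A second simulation (600 runs, marker shift fixed at 0.6 SD) gave HR 2.0 and power 48% at a 30% share, and HR 1.65 and power 27% at 50%. The Schoenfeld column takes the reduced HR as its input, so it shows what a given share costs and is no evidence for that share.

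**The case against.** Four points have weight.

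- **No marker is named as a covariate.** The preceding sentence speaks of confounding, so the intent may be narrower than the rule. A reader might infer that the plan commits to adjusting for endothelial markers. It does not; they can enter only because the rule admits all variables that pass. What remains is that the rule as published does not keep them out.
- **The total effect is not lost from the trial.** A reader might infer that the plan removes the very effect it sets out to measure, or that a real effect will be reported as absent. Kaplan-Meier, univariate Cox and direct marker comparisons do not pass through this rule, and the power statement reproduces as a plain comparison of two proportions. Only the adjusted hazard ratios are exposed.
- **The mediator evidence is limited.** It points mainly to FMD and PWV. The link from FMD to mortality comes from acute-phase data, and for arterial stiffness the outcome was in-hospital mortality. The Discussion also cites a matched study in which the FMD difference disappeared in women, in smokers and in patients with more than 3 risk factors, which bears on a kidney population. The text does not show that COVID changes intima-media thickness or bioimpedance values.
- **A prognostic model may properly contain markers.** The wording of the objectives leaves room for one. That supports a separate model, and does not support reading the marker-adjusted ratio as the COVID effect.

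That a candidate list may stand in an analysis plan not shown does not settle the matter, because a narrower list would contradict the published rule.

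**Conclusion.** The concern holds as a defect in a stated rule. Followed as written, the rule can put post-infection markers into the model that yields the adjusted COVID hazard ratio for mortality and the CV composite. That ratio would then estimate only the effect not passing through them.

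The size is unknown and depends on the assumed mediated share. At 0% nothing is lost (HR about 2.6, power about 80%). At 25% the HR is about 2.1 and power about 55%. At 50% the HR is about 1.6 and power 20-27% across the two simulations. These figures assume the planned mortality rates, a single marker and complete 24-month follow-up, and they concern mortality. The CV composite cannot be sized because the article gives no event rate for it.

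**What to change.** Replace the covariate sentence with two models.

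1. **COVID effect.** Cox model with COVID group plus a prespecified set of confounders that precede infection or that infection is unlikely to have changed: age, sex, kidney disease category or stage, diabetes, pre-existing CVD and smoking. Choose them without the univariate P < 0.05 screen. Keep the post-infection vascular, cardiac, lung, fluid and inflammatory markers out.
2. **Markers.** A separate model that adds those markers, labelled as prognostic or mediation analysis and not reported as the COVID effect.

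Baseline kidney function needs its own provision. Creatinine and proteinuria are plausible confounders within CKD stages 3-5, but no pre-infection measurement is scheduled, so barring every laboratory value would go too far. Adjust for pre-infection values where they are already on record; otherwise use the baseline values in a sensitivity analysis.

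The cost is one paragraph of analysis text, one extra model and a search of existing records for kidney function. No new patients are needed. The downside is some residual confounding where only a post-infection value of a confounder exists.
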